## Abstract

Suicidal behavior and Non-Suicidal Self-Injuries (NSSIs) are a major health problem in the adolescent population. New technologies can contribute to the development of innovative interventions in suicide prevention. Here, we present the SmartCrisis-Teen study protocol. The study consists of a randomized clinical trial which aims to evaluate the effectiveness of a digital safety plan to prevent suicidal behavior and NSSIs in adolescents. This is a multicentric study which will be conducted among the adolescent population, both in clinical and student settings, with a target sample of 1080 participants. The intervention group will receive an Ecological Momentary Intervention (EMI) consisting of a digital safety plan on their mobile phone. All participants will receive their Treatment As Usual (TAU). Participants will be followed for six months, with weekly and monthly telephone visits and face-to-face visits at three and six months. Participants will be assessed using traditional questionnaires as well as Ecological Momentary Assessment (EMA) and Implicit Association Tests (IATs). With this intervention, we expect a reduction in NSSIs through the acquisition of coping strategies and a decrease in suicidal behavior over the course of follow-up. This study provides a novel, scalable digital intervention for preventing suicidal behavior and NSSIs in adolescents, which could contribute to improving adolescent mental health outcomes globally.

## 1. Introduction

Adolescence is a complex time in life when the risk of developing mental health problems increases. Age-specific risks, the acquisition of social roles, and the search for individuation and connection to peers may lead to social insecurity, feelings of uncertainty and increased influence of the peer group on behavior [1,2]. Some authors suggest that the concept of adolescence should be extended to 18–24 years of age (the range commonly known as young adulthood) because people in this group share neurobiological characteristics with people aged 13–18 [3]. Comparing the psychopathology of both groups could shed light on this debate. While concern about adolescent mental health is by no means a new concept, worries have intensified since the COVID-19 pandemic, as an increase in the range of mental health problems, including a spike in Non-Suicidal Self-Injuries (NSSI), has been reported [4].

Among the many mental health problems that can affect young people, suicidal behavior and Non-Suicidal Self-Injury (NSSI) are receiving growing attention due to the dramatic increase observed in recent years [5]. Suicide is the second leading cause of death among people aged 10–24 years old [6], and suicide attempts impose a significant financial burden on health care systems [7]. In 2000, suicide represented 8.5% of the total deaths in the 15–24 age group in Spain, and in 2021 this percentage raised to 15.8% [8]. With regard to NSSIs, not only does they increase the risk of suicide [9], but it is also associated with other mental health problems, such as emotional dysregulation or substance use [10].

Most research in suicide prevention in adolescents is conducted in clinical settings, providing a crucial look into patients at risk of suicide. In the mid- to long-term, the most important risk factor is a history of suicidal ideation or behavior. Therefore, individuals who previously attempted or considered suicide are at higher risk of suicide-related death [11]. Secondary prevention is thus a crucial area in preventing suicide deaths [12]. However, researching suicidal behavior in school settings is also important, as the rise of NSSIs is particularly alarming in schools. As part of the EPISAM-school study, suicide risk screening was carried out in schools in the community of Madrid, where it was found that 35% of young people had self-harmed, 12.6% were at risk of suicide and 5.7% had attempted suicide [2].

The use of apps for improving mental health problems such as depression [13], substance use [14] or poor sleep [15] is spreading, and they could be particularly useful in the adolescent population, given their high digital literacy. Additionally, smartphone use among adolescents is as high as 95% [16], which makes these devices a powerful tool for improving access to mental health care.

In suicide prevention, apps can be used for risk monitoring and for intervention. Smartphone-based risk monitoring is commonly performed through Ecological Momentary Assessment (EMA), which consists of asking patients daily questions, providing a continuous, real-time source of information collected in the patient’s usual environment [17]. The therapeutic version of EMA is called Ecological Momentary Intervention (EMI), which can be used as a complementary therapeutic approach with continual availability and low cost [18] in a model that allows patients to become involved in their own treatment [19]. One of the evidence-based interventions that can be used in the form of an EMI is the Safety Plan, a set of personalized strategies aimed at dealing with a suicidal crisis [20,21]

The combination of EMA and EMI presents a therapeutic potential in suicide prevention, allowing for the possibility for the intervention to be automatically triggered when a high risk of suicide is detected. 

Another useful digital assessment tool is the Death/Suicide Implicit Association Test (D/S IAT) and the Self-Injury Implicit Association Test (S-I IAT). These tests measure the relative strength of automatic associations related to suicide, death and self-harm [22]. These IATs are brief computer-administered tests that measure reaction times when classifying semantic stimuli. In the case of the D/S IAT and the S-IIAT, the topics under consideration are life and death/suicide and self-injuries, respectively. These tests have shown high predictive power in some studies [22,23,24,25]. Finally, they have the potential to be unconscious in nature, so people have very little control over their answers.

The use of apps for the prevention of suicide behavior in the adolescent population is an area that has received little attention. Jiménez-Muñoz et al. [26] carried out a systematic review focusing on EMI interventions in suicidal behavior prevention, showing that the young population typically exhibit high rates of interest and satisfaction in these tools [27,28,29,30]. For instance, the BeyondNow application, which features a digital safety plan, underwent a successful before-and-after study on a cohort of 20 adolescent females at high risk of suicide [31]. Additionally, the BlueIce app, which concentrates on stopping self-harm, underwent a before-and-after study with a group of 44 adolescents who had a history of self-harm, leading to a decrease in self-harming actions as well as depressive symptoms and anxiety [27].

In general, the studies conducted to date have been carried out with small sample sizes and short follow-up periods. No similar studies have been conducted in Spain. Furthermore, to our knowledge, only one case series [32] and one clinical trial protocol [33] have considered the combination of EMA with EMI. Also, to our knowledge, no previous studies have combined the use of EMA or EMI with IATs. Combining different digital tools can optimize the user experience and contribute to the effectiveness of assessments and interventions. 

The SmartCrisis-Teen protocol is significant, as it offers a scalable, evidence-based digital solution that integrates Ecological Momentary Interventions (EMIs) with real-time monitoring and predictive assessments, aiming to address the growing rates of suicidal behavior and NSSIs in adolescents. This project represents a critical contribution to the field of adolescent mental health by enhancing accessibility and personalizing suicide prevention strategies.

Here, we present the SmartCrisis-Teen study protocol, a Randomized Clinical Trial whose main objective is to evaluate the effectiveness of a digital safety plan combined with EMA to prevent suicidal behavior and NSSIs in the adolescent population. Our secondary objectives are to determine the feasibility and acceptability of the safety plan and to validate the use of the D/S IAT and SI IAT with respect to the gold standard Columbia Suicide Severity Rating Scale (CSSRS) [34]. Our hypothesis, based on previous studies carried out in the adult population [35], is that there will be a significant reduction in suicidal behavior and NSSIs episodes after the follow-up, which will be translated in lower scores in the CSSRS. As a secondary hypothesis, we expect that the digital safety plan will be feasible and well-accepted and that the D/S IAT and SI IAT will demonstrate adequate external and internal validity.

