### 2.4. General Procedure:

The study involves three cohorts of participants, each followed for six months, with weekly and monthly telephone check-ins and face-to-face visits at the three-month and six-month marks. These follow-ups are crucial for assessing the intervention’s effectiveness and making any necessary adjustments to the participants’ safety plans.

After enrollment, the app is installed on the participant’s phone, and a psychologist or psychiatrist assists in setting up the app. The participants in the intervention group will be taught how to use the safety plan. 

At the end of the six-month period, participants are assessed for changes in suicidal behavior and NSSIs. The follow-up also includes a review of the participants’ use of the app, their interaction with the safety plan and satisfaction with the intervention. Figure 1 illustrate the procedure. 

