### 2.6. Procedure: High School and University Setting

In the collaborating educational centers, the study will be explained and the informed consent will be obtained for the first phase of the study, which consists of a preliminary screening using the Paykel Suicide Risk Scale [37] and the Inventory of Statements about Self-Injury scale (ISAS) that assess NSSIs [38]. Students who have tested positive will be eligible to participate in the next phase of the study.

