### 2.8. Psychometric Assessment

The assessments will be carried out by a trained psychologist. The CSSRS [34] will be used to measure suicidal behavior and suicidal ideation. Sociodemographic data will also be collected, and a satisfaction survey will be carried out.

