### 2.10. Ecological Momentary Assessment 

Digital monitoring will be carried out using the EMA methodology via the MEmind app. This app offers daily short questions that appear on the smartphone screen. Each day, a notification will appear with 2–4 random questions, which will appear at a random time during the day (from 9 a.m. to 9 p.m.) and which are part of a pool of 33 questions that make up the questionnaire. 

This questionnaire is based on the Salzburg Suicide Process Questionnaire (SSPQ) [41], the Patient Health Questionnaire-9 (PHQ-9) [42], the Positive and Negative Affect Schedule (PANA) [43], the Interpersonal Needs Questionnaire (INQ) [44], and previous EMA studies [45,46,47,48]. 

Questions will remain as a notification on the screen until they are answered. The application also has a free text field in which the participant can write comments on their status.

The EMA questions belong to six categories:Suicidality: 4 questions;Non-suicidal self-injury: 2 questions;Affect: 9 questions;Interpersonal experiences: 11 questions;Sleep: 4 questions;Apetite and eating: 3 questions.

The complete list of Ecological Momentary Assessment (EMA) questions can be found in Appendix A.

The digital safety plan is incorporated into the MEmind app and consists of a set of personalized coping strategies that the participant can use in the event of a suicidal crisis [20]. The original safety plan was designed by Stanley and Brown (2012) [20] and has been proven in several studies to decrease the risk of suicide [21]. 

It should be designed with the help of clinical staff. The safety plan will take advantage of smartphones by offering participants the ability to call loved ones, show relaxation videos, activate pre-recorded messages, link to websites with health resources, or connect the participant to emergency resources. During the first visit, the safety plan will be customized with the participant based on their personal preferences (e.g., by providing a list of emergency contacts or programming the app to trigger a song, image or video pre-selected by the participant).

The tabs of the safety plan are: 

The security plan consists of 7 tabs. In each tab, the patient can add text messages, voice messages, audios, photos, videos and links to websites.

The 7 tabs in the security plan are as follows:

1. Warning Signs—warning signs (thoughts, images, moods, situations, behaviors, etc.…) that may indicate a crisis is occurring.

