### 2.12. Assessment Criteria

After six months, a before-and-after comparison will be made in both the control and intervention groups. 

Our main outcome will be a reduction in suicidal behavior, as measured by a score on the CSSRS.

Our secondary outcomes will be as follows: The occurrence of suicidal behavior as a clinical event (completed suicide, attempted suicide, ED visit for suicidal ideation, ED visit for self-harm),Predictive validity of the D/S IAT and SI IAT tests to clinical events recorded during follow-up.Acceptability of the project through user-perceived satisfaction.Project feasibility measured by participation and retention.

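### NSSI is half of the main objective, but no listed outcome is NSSI occurrence or frequency, and the NSSI data that would be collected are tied to no analysis

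*Protocol article*

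**What the plan says.** The Introduction gives the main objective as to "evaluate the effectiveness of a digital safety plan combined with EMA to prevent suicidal behavior and NSSIs in the adolescent population". The hypothesis there is a "significant reduction in suicidal behavior and NSSIs episodes after the follow-up, which will be translated in lower scores in the CSSRS". Section 2.4 adds: "At the end of the six-month period, participants are assessed for changes in suicidal behavior and NSSIs". Section 4 (Expected Results) lists a fall in NSSI as the second of two expected benefits.

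The measurement side reads differently:

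- **Primary outcome (section 2.12):** "Our main outcome will be a reduction in suicidal behavior, as measured by a score on the CSSRS". Section 2.8 says the CSSRS "will be used to measure suicidal behavior and suicidal ideation", and section 2.11 describes it in the same terms. Neither mentions NSSI.
- **Secondary outcomes (section 2.12):** the only entry touching self-injury is the last component of "The occurrence of suicidal behavior as a clinical event (completed suicide, attempted suicide, ED visit for suicidal ideation, ED visit for self-harm". The other entries are IAT predictive validity, acceptability and feasibility.
- **Time-to-event analysis (section 2.13):** the event is suicide, attempt, or an emergency visit for ideation. The self-harm visit is absent.
- **ISAS:** section 2.6 places it in the first phase in the educational centers, "which consists of a preliminary screening using the Paykel Suicide Risk Scale [37] and the Inventory of Statements about Self-Injury scale (ISAS". Section 2.11 repeats it under screening and does not include it among the assessment instruments.
- **EMA (section 2.10, Appendix A):** "Each day, a notification will appear with 2–4 random questions", drawn from a pool of 33. Two items concern NSSI: one on the act (yes/no, past 24 hours) and one on the urge (1–5, since the last prompt).

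**The concern.** A main objective with two targets needs at least one outcome for each. Here every named efficacy outcome concerns suicidal behavior. A recent NSSI alone qualifies a patient for cohort 1, and the app carries a dedicated NSSI-crisis module. A participant enrolled for NSSI could improve a great deal, or not at all, without any listed outcome being designed to register it.

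Two things are at stake. First, a conclusion about NSSI would have to rest on an analysis chosen after the data are in, or on a CSSRS score that the article describes as measuring something else. Second, the Self-Injury IAT would be validated against criteria that fit self-injury poorly.

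**Working it through.** **Step 1. Objective set against outcomes.**

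| Where | NSSI? |
|---|---|
| Section 1, objective and hypothesis | Yes, alongside suicidal behavior |
| Section 2.4, six-month assessment | Yes, no instrument named |
| Section 4, expected results | Yes, as a separate second benefit |
| Section 2.12, primary outcome | No |
| Section 2.12, secondary outcomes | Only self-harm that leads to an emergency visit, filed under suicidal behavior |
| Section 2.13, event definition | No, the self-harm visit is omitted |
| Section 2.13, other analyses | None names NSSI |

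The article is also inconsistent on what the CSSRS will show. Section 1 expects fewer NSSI episodes to appear as lower CSSRS scores. Section 4 ties lower scores to ideation and attempts, and lists NSSI apart.

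**Step 2. Participants with no listed NSSI scale.** Section 2.3 plans 120 per center and 120 × 9 = 1080. Seven hospitals form cohort 1 (section 2.2.1), so I read the nine as seven hospitals plus two educational settings. Cohort 1 is then 7 × 120 = 840, and 840/1080 = 78%. The ISAS is not listed for this cohort at any time. In the other two cohorts it is listed once, before enrollment.

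**Step 3. How often the EMA asks about NSSI.** The pool reproduces: 4 + 2 + 9 + 11 + 4 + 3 = 33. The article says only that questions are random, so I assume equal-probability draws without replacement within a day, k = 2, 3 or 4 questions a day, 182 days and full response.

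- Daily chance of the act item = k/33.
- Expected askings = 182 × k/33.
- Daily chance of either NSSI item = 1 − C(31,k)/C(33,k).

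| k | Act item | One day in | Askings in 182 days | Either item |
|---|---|---|---|---|
| 2 | 2/33 = 6.1% | 16.5 | 11.0 | 11.9% |
| 3 | 3/33 = 9.1% | 11 | 16.5 | 17.6% |
| 4 | 4/33 = 12.1% | 8.25 | 22.1 | 23.1% |

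The act item looks back only 24 hours, so most days of follow-up are never asked about. The urge item covers the impulse, not the act.

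**The case against.** Four points on the other side deserve weight.

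**NSSI is not wholly unmeasured.** A reader might infer that nothing in follow-up measures NSSI. The documents do not support that. All participants receive the EMA, which has two NSSI items, and an emergency visit for self-harm is a partial outcome. Section 2.4 also states that change in NSSI is assessed. What stands is narrower: no outcome is NSSI occurrence or frequency, and no analysis uses the EMA items.

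**Sparse EMA sampling does not rule out a comparison.** At three questions a day, a participant with four separate NSSI days has a (1 − 3/33)^4 = 68% chance that none is asked about (60% to 78% for four to two questions a day), if draws are independent across days. A reader might conclude that the EMA is useless for NSSI. That does not follow. Comparing arms needs a fair sample of days, not every event. With 540 per arm, 540 × 16.5 gives about 8,900 asked person-days per arm at full response (about 6,000 to 11,900 across the range). The gap is that the plan does not use these data.

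**The Self-Injury IAT has stated criteria.** They are the CSSRS (sections 1 and 4) and clinical events (section 2.12). They suit NSSI poorly, but it would be wrong to say that there are none.

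**An article condenses a protocol.** The instrument behind section 2.4 may be in the full document, and whether a CSSRS score reflects NSSI cannot be settled from the article. I accept both. But section 2.12 sets out the outcomes one by one, and section 2.11 lists the instruments down to the seven satisfaction questions. What they state does not match the objective. An analysis plan cannot recover data that were not collected.

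**Conclusion.** The point holds in this form: NSSI is half of the main objective and hypothesis, but no primary or secondary outcome is NSSI occurrence or frequency. The one related endpoint misses any NSSI that does not reach an emergency department, does not separate intent, and drops out of the time-to-event definition. The ISAS is listed only at educational screening, leaving 78% of the planned sample without a listed NSSI scale. The EMA act item appears on 6% to 12% of days and feeds no stated analysis. Followed as written, the plan would not test the NSSI half.

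The 78% rests on reading the nine centers as seven hospitals plus two educational settings. The EMA figures rest on equal-probability draws, 182 days and full response; lower response would reduce the number of askings. The mismatch between objective and outcomes depends on none of these.

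**What to change.** 1. Name one NSSI outcome (occurrence or frequency) as a secondary outcome. State its instrument, recall window and time points for all three cohorts at the existing baseline, three- and six-month visits. The ISAS is one candidate, but the article does not give its recall period or scoring, so its suitability for measuring change should be checked first. A short NSSI frequency question with a stated recall window is another.
2. Compare that outcome between arms, adjusted for baseline.
3. Add a between-arm analysis of the EMA act item, as the proportion of asked days with NSSI.
4. Use the NSSI outcome as an added criterion for the Self-Injury IAT.
5. Reconcile sections 1, 2.4, 2.12, 2.13 and 4, including whether the CSSRS score is meant to reflect NSSI and whether the self-harm visit belongs in the time-to-event definition.

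If items 1 and 2 are not wanted, remove NSSI from the main objective and hypothesis.

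Optionally, ask the EMA act item on a fixed schedule or with a longer look-back. A fixed daily slot is not free. Each other item would fall from 2/33 to 1/32 (48% less), from 3/33 to 2/32 (31% less) or from 4/33 to 3/32 (23% less), and this includes the four suicidality items. A longer look-back avoids that loss at the price of longer recall.

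The main change costs a few minutes of questionnaire at visits that already occur.

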### 2.9. Implicit Association Test

The Spanish versions of the SI-AT and D/S-IAT [39] will be administered. These are 5 min tests administered by computer. The D-S IAT requires participants to match words from the following two semantic fields: “death” (die, dead, deceased, lifeless, and suicide) and “life” (alive, survive, live, thrive, and breathing). The attributes “me” (I, myself, my, self, and mine) and “not me” (they, them, their, theirs, and other) are used to categorize the words. The reaction times are processed using the standard D algorithm for IATs [40]. The algorithm takes into account the reaction time for the implicit association with death (faster reaction scores positively) and the reaction time for the implicit association with life (faster reaction scores negatively). Therefore, a participant with an unconscious bias towards life will have a negative score and a person with an unconscious bias towards death will have a positive score. The greater the score, the stronger the association in one direction or the other. A similar principle is applied for the SI-IAT, albeit using semantic fields related to self-harm. 

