### 2.11. Assessments: Questionnaires 

The assessments will be conducted by psychologists and/or psychiatrists, except for the screening in schools, which will be self-administered and carried out by the participant. All questionnaires will be completed in the MEmind collection portal, which allows for easy completion and immediate uploading to databases. 

The screening will consist of the completion of the following two short scales: Paykel Suicide Risk Scale [36];Inventory of Statements about Self-Injury scale (ISAS) [37].

The following questionnaires and instruments will be used for the assessment of items related to suicidal behavior and suicide ideation:Sociodemographic data including gender, age, family socioeconomic status, grade repetition, sexual orientation, number of siblings (including the participant) and child adoption.The Columbia Suicide Severity Rating Scale (CSSRS) [34] will be administered to measure suicide ideation and behavior. This scale will be employed both in the basal and the follow-up appointments.In addition, we will verify suicide attempts and suicide deaths through the digital medical record (clinical events).The Inventory for Depressive Symptomatology—Clinical (IDSC-30) scale [49] will be administered in order to measure depressive signs and symptoms.MacLean Screening Instrument for Borderline Personality Disorder [50].The Spanish version of the Death/Suicide Implicit Association Test (D/S-IAT) [38]Satisfaction surveys (one qualitative and one quantitative satisfaction survey).

The quantitative survey consists of the following questions, which participants will rate from 1 to 10:

1. Please rate your overall satisfaction with the application.

2. Is the application easy to use? 

3. Is the performance of the application good (speed of navigation, accuracy, lack of errors...)?

4. How do you rate the quality of the graphics?

5. How secure is the application with regard to the processing of personal data?

6. To what extent does the application have a clinical benefit? 

7. Would you be willing to recommend this application to family or friends?

The qualitative survey will ask the participant to comment on how their participation in the project has been, what aspect they liked most, what aspect they liked least and what suggestions they have for improvement, as well as any additional comments they may wish to make. 

Both surveys will be carried out at the six-month visit. 

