## 4. Expected Results

This project is highly feasible, as the mobile application it uses has already been tested in previous studies in the adult population [35]. With this intervention, we hope to contribute to the mental health of the adolescent population in the following two ways: Firstly, by decreasing suicidal behavior over the course of follow-up, i.e., both suicidal ideation and suicide attempts, which will be reflected in lower CSSRS scores in the intervention group. Secondly, by reducing NSSIs through the acquisition of coping strategies that can be used in times of risk. This training should be a useful tool beyond the follow-up period of the study and could be applied in the long term. As NSSIs increase the risk of a subsequent suicide attempt, it is hoped that reducing NSSI episodes will also reduce suicide risk.

We also expect that The D/S IAT and SI IAT will demonstrate predictive validity with respect to the gold standard CSSRS.

Finally, we also expect the project to be well accepted by the participants, which will be reflected in the satisfaction surveys provided. Demonstrating its feasibility will allow it to be implemented on a large scale.

Monitoring will be a source of information for understanding suicidal behavior, NSSIs and their associated factors. Real-time monitoring will facilitate an individualized approach that will allow for the design of prevention strategies tailored to the uniqueness of each patient. 

Finally, it is important to stress the importance of transmitting to the adolescent population the need to seek help if they find themselves in a situation of suicidal risk. Given that this is a population that integrates mobile devices into their daily lives, it is expected that the demand for help will be more accessible; it is also hoped that the reception of the preventive approach will be improved.

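### The self-injury IAT is validated only against suicidality criteria: no NSSI measure is named as its criterion, although NSSI data are collected

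*Protocol article*

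**What the plan says.** **The tests.** The Introduction gives the two tests different topics: life and death or suicide for the D/S-IAT, self-injury for the SI-IAT. Section 2.9 describes the death/life word task and adds: "A similar principle is applied for the SI-IAT, albeit using semantic fields related to self-harm".

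**The criteria.** The Introduction states one aim for both tests: "to validate the use of the D/S IAT and SI IAT with respect to the gold standard Columbia Suicide Severity Rating Scale (CSSRS". Section 4 repeats it, saying that the D/S IAT and the SI "IAT will demonstrate predictive validity with respect to the gold standard CSSRS". Section 2.12 lists a second criterion: "Predictive validity of the D/S IAT and SI IAT tests to clinical events recorded during follow-up".

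**What the CSSRS is for.** Section 2.8 says that it "will be used to measure suicidal behavior and suicidal ideation". Section 2.11 says the same: "The Columbia Suicide Severity Rating Scale (CSSRS) [34] will be administered to measure suicide ideation and behavior".

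**Where NSSI is measured.** Section 2.6 uses "the Inventory of Statements about Self-Injury scale (ISAS) that assess NSSIs" in the preliminary screening of the high school and university cohorts. Section 2.10 and Appendix A include two NSSI questions in the EMA, which section 2.1 gives to every participant. Section 2.4 says that change in NSSI is assessed at six months but names no instrument.

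**The instrument list.** Section 2.11 names a single IAT: "The Spanish version of the Death/Suicide Implicit Association Test (D/S-IAT) [38". Section 2.9 says that both tests will be given, and section 2.12 has both as an outcome.

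**The concern.** A validation study needs a criterion that contains the construct the test claims to measure. Here two tests with different constructs share one pair of criteria, and both criteria are built around suicidality. That suits the D/S-IAT. For the SI-IAT neither likely result is clear:

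- If the association is weak, the test may be poor, or its target may be largely absent from the criterion. The planned comparison cannot separate the two.
- If the association is strong, the test tracks suicidality, which is already the D/S-IAT's role. Validity for self-injury would still be undemonstrated.

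Preventing NSSI is half of the trial's main objective, so readers will want to know whether the SI-IAT says anything about NSSI itself.

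**Working it through.** The article gives no figure for this point, so the check is mainly a comparison of sections, with one calculation on how dense the available NSSI data are.

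**Step 1. Criteria against construct**

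| Measure | Where and for whom | Covers NSSI? | Named as SI-IAT criterion? |
|---|---|---|---|
| CSSRS | 2.8, 2.11; baseline and follow-up | Not in the article's description | Yes (1, 4) |
| Clinical events | 2.12 | Only through emergency visits for self-harm, not split by intent | Yes (2.12) |
| Two EMA NSSI items | 2.1, 2.10, Appendix A; both arms, all cohorts | Yes | No |
| ISAS | 2.6, 2.11; educational screening | Yes | No |
| Six-month assessment of NSSI change | 2.4; instrument not named | Yes | No |

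The measures named as criteria are those that cover NSSI least.

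**Step 2. Is the event criterion stable?** Three sections describe events differently:

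- Section 2.11 checks the medical record for suicide attempts and deaths.
- Section 2.12 adds emergency visits for suicidal ideation and for self-harm.
- Section 2.13 defines the survival event as suicide, attempt, or an emergency visit for ideation, with no self-harm component.

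The one component that could contain NSSI is thus present in one of the three. Even there it misses self-injury that never reaches an emergency department.

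**Step 3. Reach of the ISAS.** Section 2.3 plans nine blocks of 120, and section 2.2.1 names seven hospitals. The split between settings is inferred from these, not stated:

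- clinical: 7 × 120 = 840 of 1080 (78%), for whom the ISAS is not listed;
- educational: 2 × 120 = 240, for whom it is listed at screening only.

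**Step 4. Density of the EMA self-harm item.** Inputs: 2 to 4 questions per day from a pool of 33 (section 2.10), and six months of follow-up, taken as 182 days (assumption). The category counts reproduce the stated pool: 4 + 2 + 9 + 11 + 4 + 3 = 33. Assuming equal random draws, the item appears on a given day with probability q/33, and the expected number of showings is 182 × q/33:

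- q = 2: 2/33 = 6.1% of days; 182 × 2/33 = 11.0 showings
- q = 3: 3/33 = 9.1% of days; 182 × 3/33 = 16.5 showings
- q = 4: 4/33 = 12.1% of days; 182 × 4/33 = 22.1 showings

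The item looks back 24 hours, so a single isolated day of self-injury would be picked up with a chance of roughly 6% to 12%, even if every prompt is answered. NSSI data during follow-up therefore exist for all participants, but they are thin.

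**The case against.** The strongest reply is that the plan can be read literally. It asks how the SI-IAT relates to the CSSRS and to clinical events. Whether an implicit self-harm measure predicts suicidal outcomes is a coherent question, since the Introduction and section 4 both say that NSSI raises suicide risk. The Introduction also expects fewer NSSI episodes to show as lower CSSRS scores, and the form of the CSSRS to be used is not shown. An unseen full protocol or SAP could name a further criterion. The issue touches one test within one secondary objective and leaves the effectiveness comparison untouched.

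Much of this stands. The literal question is legitimate, but it concerns association with suicidality. Calling the CSSRS the gold standard for a self-harm test claims more than that. The link between NSSI and CSSRS scores is a hypothesis and does not describe what the scale measures. The criterion is not simply left out by condensation: the article states it in sections 1, 2.12 and 4, each time jointly for both tests.

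Three stronger readings are tempting, and the document does not support them:

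- **Neither criterion captures any NSSI.** Section 2.12 includes emergency visits for self-harm, and whether the CSSRS form used has an NSSI item cannot be settled from the article.
- **Validity for self-injury cannot be estimated, because no participant has NSSI data in follow-up.** Every participant gets the EMA with its two NSSI items, and section 2.4 foresees an NSSI assessment at six months. What can be said is that the ISAS, the only NSSI scale listed, is not scheduled after screening.
- **The SI-IAT will not be collected.** Section 2.9 says that it will be given. The section 2.11 list is introduced as covering suicidal behavior and ideation and also leaves out the EMA, so the omission is an inconsistency to reconcile and does not show that the test was dropped.

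**Conclusion.** The stated criteria do not match the construct of the SI-IAT, and no NSSI measure is named to fill the gap. As written, the trial can report how the SI-IAT relates to suicidal ideation, suicidal behavior and clinical events. It has not planned the comparison that would show validity for self-injury. The data for a partial answer are already being collected: about 11 to 22 showings of the self-harm item per participant, assuming equal random draws, 182 days and full response. Lower response would reduce this.

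The conclusion rests on the article's own description of the CSSRS and on no assumption about its items. It is a moderate point: it affects the interpretation of one secondary objective, is cheap to correct, and does not bear on the primary comparison. The differences between sections on the list of IATs and on the event definition are separate, smaller inconsistencies that feed into the same analysis.

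**What to change.** 1. State a criterion for each test. Keep the CSSRS and suicidal clinical events for the D/S-IAT.
2. For the SI-IAT, add an NSSI criterion. At minimum, use the EMA 24-hour self-harm item, with a rule for summarizing it per participant that allows for the varying number of showings. This needs wording only.
3. Preferably also give the ISAS at the baseline and six-month visits in all three cohorts, with a fixed look-back. Section 2.11 already has it completed in the trial's portal and both visits exist, so the cost is a few more minutes of questionnaire time per visit.
4. If neither is adopted, reword the SI-IAT aim and limit its conclusion to association with suicidal ideation and behavior.
5. Reconcile the section 2.11 list, which names only the D/S-IAT, with sections 2.9 and 2.12.
6. Align the event definitions in sections 2.11, 2.12 and 2.13 on whether self-harm counts, and state which definition the IAT analysis uses.
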